## Abstract

**Background:**

Bronchiolitis is the most common reason for admission to hospital for infants less than one year of age. Although management is well defined, there is substantial variation in practice, with infants receiving ineffective therapies or management. This study will test the effectiveness of tailored, theory informed knowledge translation (KT) interventions to decrease the use of five clinical therapies or management processes known to be of no benefit, compared to usual dissemination practices in infants with bronchiolitis. The primary objective is to establish whether the KT interventions are effective in increasing compliance to five evidence based recommendations in the first 24 h following presentation to hospital. The five recommendations are that infants do not receive; salbutamol, antibiotics, glucocorticoids, adrenaline, or a chest x-ray.

**Methods/design:**

This study is designed as a cluster randomised controlled trial. We will recruit 24 hospitals in Australia and New Zealand, stratified by country and provision of tertiary or secondary paediatric care. Hospitals will be randomised to either control or intervention groups. Control hospitals will receive a copy of the recent Australasian Bronchiolitis Guideline. Intervention hospitals will receive KT interventions informed by a qualitative analysis of factors influencing clinician care of infants with bronchiolitis. Key interventions include, local stakeholder meetings, identifying medical and nursing clinical leads in both emergency departments and paediatric inpatient areas who will attend a single education train-the-trainer day to then deliver standardised staff education with the training materials provided and coordinate audit and feedback reports locally over the study period. Data will be extracted retrospectively for three years prior to the study intervention year, and for seven months of the study intervention year bronchiolitis season following intervention delivery to determine compliance with the five evidence-based recommendations. Data will be collected to assess fidelity to the implementation strategies and to facilitate an economic evaluation.

**Discussion:**

This study will contribute to the body of knowledge to determine the effectiveness of tailored, theory informed interventions in acute care paediatric settings, with the aim of reducing the evidence to practice gaps in the care of infants with bronchiolitis.

**Trial registration:**

Australian New Zealand Clinical Trials Registry ACTRN12616001567415 (retrospectively registered on 14 November 2016).

## Background

Knowledge translation (KT) in emergency medicine is a relatively new field, and in paediatric emergency medicine (PEM) is in its infancy. There have been several trials assessing the effectiveness of various strategies for KT in emergency medicine and in PEM, although none of these were conducted in Australia or New Zealand [1, 2]. Approaches to KT are varied and, it is likely that barriers and challenges experienced in one region or country are not necessarily experienced in another, resulting in the need to contextualise KT evidence to local environments. A recent systematic review of KT studies in PEM concluded that more optimal study designs with explicit descriptions of implementation were needed to enhance our understanding of how best to translate evidence in to practice [3].

Bronchiolitis is an appropriate condition for testing the effectiveness of KT implementation strategies for a number of reasons; 1. It is an extremely common disease that is seen in small rural hospitals as well as in tertiary paediatric centres [4–6]; 2. It is the most common reason for admission to hospital for infants aged < 1 year. In New Zealand, there are > 70 admissions/1000 infants. Māori (relative risk (RR) 3.0), Pacific (RR 4.3), and those living in the most deprived quintile (RR 4.7) are at most risk [7, 8]; In Australia; bronchiolitis accounts for 56% of all admissions of infants aged less than one year [9]; 3. Hospitalisation is the primary determinant of health care expenditures for the disease [10]; 4. Management is well defined [11, 12]; and necessitates supportive care of oxygen and supplemental hydration with medical and nursing involvement [13, 14]; 5. Substantial variations in practice have been shown to occur [15]. Therefore, effective KT implementation strategies should lower unnecessary health care interventions, improve patient care and allow reallocation of healthcare funds to other areas.

The Paediatric Research in Emergency Departments International Collaborative (PREDICT) network [16] is well placed to undertake this study having completed a multi-centre randomised controlled trial (RCT) of intravenous versus nasogastric fluid replacement in children admitted with bronchiolitis [13, 14, 17–19]. As part of this trial, data were collected on > 3800 admissions for bronchiolitis, over three years from seven Australasian sites. These data show that five therapies and management processes, for which there is high-level evidence that they are ineffective, were used at least once in 27 to 48% of bronchiolitis admissions [20]. Ineffective interventions included inhaled salbutamol, inhaled adrenaline, oral glucocorticoids, antibiotics and chest x-ray.

Having identified both inappropriate care and variation in care, an Australasian Bronchiolitis Guideline for the management of bronchiolitis was developed, providing evidence and recommendations for emergency department (ED) and paediatric inpatient care, with widespread stakeholder endorsement [21]. Guidelines can be formally defined as “systematically developed statements to assist practitioners and patient decisions about appropriate care for specific clinical circumstances” [22]. It is recognised that to effectively manage conditions there needs to be agreement from all specialty groups within individual hospitals involved in care for the condition of interest. Thus, the Australasian Bronchiolitis Guideline was developed using a consensus process across both countries utilising craft groups and specialists from both the ED and paediatric inpatient units involved in management of infants with bronchiolitis. Recommendations from this guideline will be implemented using tailored, theory informed KT interventions in this study as it is now accepted that simply providing such a guideline to clinicians is insufficient to significantly change practice [23].

Using a theoretical approach to develop KT interventions is increasing considered to be best practice [24]. Tailored interventions (interventions planned following investigation into the factors that influence practice and reasons for resisting practice change) are more likely to improve practice than no intervention [25]. Cochrane Effective Practice and Organisation of Care systematic reviews have shown that: Interventions consistently showing effectiveness include audit and feedback [26], interactive educational meetings, educational outreach visits, reminders (either manual or computerised) and multifaceted interventions (defined as a minimum of two combined interventions); Interventions that have shown some improvement include the use of local champions and local consensus processes and patient-mediated interventions; Interventions that consistently show little or no effect are didactic educational meetings and educational materials such as those distributed for recommendations of clinical care, including practice guidelines, electronic publications and audio-visual materials [27, 28]. However, there is little evidence on the effectiveness of interventions in PEM settings.

We are therefore undertaking a cRCT to determine if tailored, theory informed KT interventions are effective in improving evidence-based practice in Australasian paediatric acute care settings.

## Methods

### Aim

The aim of the study is to test the effectiveness of tailored, theory informed KT interventions at increasing the uptake of five evidence-based recommendations from the Australasian Bronchiolitis Guideline [14]. The five key recommendations from the guideline are that infants under one year of age with bronchiolitis who present to hospital receive none of the following: 1. Salbutamol; 2. Antibiotics; 3. Glucocorticoids; 4. Adrenaline; 5. A chest x-ray (see Table 1).

**Table 1 Tab1:** Key clinical recommendations from the Australasian Bronchiolitis Guideline

Clinical intervention	NHMRC strength of recommendation	GRADE quality of evidence	Guideline recommendation
Salbutamol	A	Strong	Do not administer salbutamol
Antibiotics	B	Conditional	Do not use antibiotics
Glucocorticoids	B	Strong	Do not administer systemic or local glucocorticoids (nebulised, oral, intramuscular or intravenous)
Adrenaline	B	Strong	Do not administer adrenaline (nebulised, intramuscular or intravenous)
Chest x-ray	D	Conditional	Chest x-ray is not routinely indicated

*NHMRC* National Health and Medical Research Council, *GRADE* Grading of Recommendations, Assessment, Development and Evaluations

### Research objectives

The primary objective is to determine the effectiveness of tailored, theory informed KT interventions versus passive dissemination of a bronchiolitis guideline in decreasing use of therapies and management processes known to be of no benefit in infants with bronchiolitis.

Secondary objectives include evaluating the effectiveness of the interventions at decreasing duration of hospital stay for infants with bronchiolitis and determining their relative effectiveness in tertiary paediatric and secondary hospitals. In addition we will also quantify health care costs (including cost associated with guideline development and implementation) and measure change in median medication doses.

Integral to our primary objective is the need to evaluate the fidelity of the KT interventions and assess receipt, delivery and acceptability of the KT interventions by conducting a process evaluation.

### Design

This is a multi-centre cRCT where the hospitals, ED and paediatric inpatient staff members, represent the units of randomisation. A randomised design is advantageous in evaluating the effectiveness of an intervention since bias is minimised when estimating intervention effects compared with other study designs [29, 30]. Clusters have been chosen for the following reasons: 1) the intervention is targeted to the staff involved in the care of infants with bronchiolitis, 2) the hospitals represent distinct non-independent patient populations in both geographical areas and levels of paediatric service provision, and 3) a RCT involving randomisation at the level of the patient is impractical [31, 32]. The study design is outlined in Fig. 1.

**Fig. 1 Fig1:**
[figure not shown]
KT study process design*Site visit to include: meeting clinical directors, discussion re study requirements, ethics and the departmental agreement. KT = Knowledge Translation. HREC = Health Research Ethics Committee

### Recruitment and eligibility

#### Recruitment of hospitals and inclusion/exclusion criteria

Hospitals will be identified in two ways; through the members of the PREDICT research network and from the Australasian College for Emergency Medicine ED Directory list of 24 h Australasian EDs (regional and metropolitan) until a total of 24 hospitals are recruited (six New Zealand and 18 Australian hospitals), ensuring selection across different states and hospitals that provide different levels of paediatric care. Hospitals who have principal or co-investigators in this study, or who had clinicians with significant involvement in the writing of the Australasian Bronchiolitis Guideline will be excluded to reduce the potential risk of bias in the study results.

Following initial contact, a recruitment pack detailing the proposed study will be sent to both clinical directors and nursing managers of ED and paediatric inpatient areas. A recruitment meeting will follow (via telephone or face-to-face) to discuss details and logistics of the study (with expectations of hospitals as well as the study team detailed). A baseline checklist will be completed to quantify annual bronchiolitis presentation numbers.

**Inclusion criteria for hospitals:**
Have a confirmed ED census of > 135 bronchiolitis presentations per year.Be willing to participate and abide by the randomisation schedule (either control or intervention).A signed department agreement by both ED and paediatric inpatient clinical directors.Have the ability to collect the required retrospective patient data from clinical notes.

**Exclusion criteria for hospitals:**
Inability to audit clinical notes.Be averse to participating if randomised to the control arm.Those hospitals having clinicians who are principal or co-investigators in this study or had significant involvement in the writing of the Australasian Bronchiolitis Guideline.

### Randomisation and allocation concealment

Randomisation of hospitals into either intervention or control groups will be completed using randomisation Stata 14.2 statistical software, by a statistician not affiliated with the study. Stratification will be undertaken by country (Australia and New Zealand) as well as whether the hospital is a tertiary or secondary paediatric hospital. A hospital will be classified as tertiary if they have a dedicated paediatric intensive care unit.

### Blinding

Due to the nature of the intervention, it will not be possible to blind staff members involved in the study to group allocation. This is a potential threat to the validity of the study. Communication between intervention and control groups will be discouraged but still may occur.

Ideally hospitals will use local data collectors not associated with patient care in ED or paediatric inpatient areas and who are not aware of study outcomes. The data collection training will focus on the operational aspects of the study. A percentage of data collection at each site will be independently audited to confirm the authenticity of the data.

### Knowledge translation interventions

#### Intervention groups

Hospital intervention groups will receive tailored, theory informed KT interventions. A stepped approach will be followed to develop the interventions including: identifying five key evidence-based recommendations from the bronchiolitis guideline as well as using findings from a previous qualitative study where clinicians were interviewed to identify factors perceived to influence the management of infants with bronchiolitis. The interview schedule was developed and interviews analysed using the Theoretical Domains Framework (TDF) which describes a comprehensive structure of 14 theoretical domains from 33 behaviour change theories and 128 constructs. The TDF has demonstrated strong explanatory and predictive powers across a number of healthcare settings with helpfulness in advising interventions to improve practice change [33, 34]. This framework has recently been successfully trialled in an Australian ED environment to understand factors influencing the management of mild traumatic brain injury in adults to then guide intervention development [35]. Thematic analysis findings from the qualitative interviews will be mapped to behaviour change techniques with interventions being developed to address influencing factors. Table 2 summarises the intervention components of this protocol.

**Table 2 Tab2:** Planned delivery of the intervention

All interventions	Intervention site	Control site
Electronic and printed copy of complete Australasian Bronchiolitis Guideline	✓	✓
Electronic and printed copy of summarised bedside clinical Australasian Bronchiolitis Guideline	✓	✓
Multidisciplinary key stake holder meeting to create organisational buy-in	✓	
Identification of up to four clinical leads (medical and nursing) from ED and paediatric inpatient areas	✓	
One day train-the-trainer workshop for clinical leads	✓	
Provision of KT materials for local training • Educational power points • Fact sheets • Posters • Parent / caregiver information sheet	✓	
Monthly audit and feedback site reports	✓	
KT study manual	✓	
Support for clinical leads during intervention period by key research group contact	✓	

*ED* emergency department, *KT* knowledge translation

#### Control groups

Hospitals in the control group will receive an electronic and printed copy of the complete Australasian Bronchiolitis Guideline as well as the summarised bedside clinical version. At the end of the study (after effectiveness data collection has occurred), control hospitals will be offered a one day training day which will cover similar content to that which the intervention groups received.

#### Research outcomes

Primary outcome

Compliance or non-compliance for each patient presentation with the guideline during the first 24 h following presentation to ED (acute care period), with regards to the use of five key therapies and management processes known to have no benefit (salbutamol, antibiotics, glucocorticoids, adrenaline and chest x-ray).

Secondary outcomesCompliance or non-compliance for each patient presentation with the guideline with regards to the use of key therapies and management processes known to have no benefit (salbutamol, antibiotics, glucocorticoids, adrenaline and chest x-ray):While in ED.While an inpatient.During total hospitalisation.Compliance or non-compliance for each patient presentation with guideline recommendations during the first 24 h following presentation to the ED (acute care period) with regards to the use of:Salbutamol.Antibiotics.Glucocorticoids.Adrenaline.Chest x-ray.Compliance or non-compliance for each patient presentation with guideline recommendations during their total hospitalisation with regards to use of:Salbutamol.Antibiotics.Glucocorticoids.Adrenaline.Chest x-ray.Process evaluation including measure of receipt, delivery and acceptability.Length of stay.Death and or intensive care admission.Health care costs (including cost associated with guideline development and implementation).Median number of medication doses:In acute care period.During total hospitalisation.

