#### Sample size

The primary outcome of this study is compliance to the Australasian Bronchiolitis Guideline in regards to the five therapies and management processes known to have no benefit.

The sample size calculation is bound by the assumption of an absolute increase in compliance to the guideline of at least 15% in the intervention arm compared to the control arm in which, according to preliminary data, compliance to the guideline is assumed to be close to 50%. The rationale for selecting an absolute increase in compliance of 15% is that it is both clinically relevant and also justifies the resource associated with delivery of the intervention. A sample size of 1620 infants per arm (3240 in total) is required to provide 82% power (alpha = 0.05) to detect a minimum difference of 15% in compliance with the guideline, allowing for an average intra-class correlation coefficient of 0.055 (based on previous data from seven Australian Hospitals [20]) and an average cluster size of 135 (24 clusters in total).

The sample size calculations took the nature of the outcome (binary variable outcome variable: guideline compliance yes/no) as well as the issue of clustering (heterogeneity in estimated proportions between sites that exceeds variability being explained by random sampling) into account.

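### Taken over all presentations, the median number of medication doses is expected to be 0 in the intervention arm and 0 or on the edge of 0 in control, so it says little about dosing

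*Protocol article*

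**What the plan says.** The last item under Research outcomes is "Median number of medication doses", once for the acute care period (the first 24 h) and once for the total stay. Research objectives has the matching aim, to "measure change in median medication doses". Neither place gives the denominator (all sampled presentations or only infants given a drug), nor says whether doses are counted for each drug or pooled.

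The figures that bear on the median are elsewhere in the article:

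- Sample size takes control compliance from preliminary data: "compliance to the guideline is assumed to be close to 50" per cent. The effect sought is an "absolute increase in compliance to the guideline of at least 15% in the intervention arm".
- The Abstract defines what compliance covers: "The five recommendations are that infants do not receive; salbutamol, antibiotics, glucocorticoids, adrenaline, or a chest x-ray". Four of these items are drugs and the fifth is imaging.
- The Background reports that, at seven sites in an earlier trial, the five items "were used at least once in 27 to 48% of bronchiolitis admissions".
- The list of patient data to be collected includes the number and timing of doses for each of the four drugs.

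**The concern.** A median is 0 whenever at least half the infants have no dose, however many doses the others receive. The plan expects about half of control infants, and about two thirds of intervention infants, to receive none of the five items. Infants who had only a chest x-ray also have no drug dose. A median over all presentations therefore sits at or near 0 in both arms.

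The protocol names this statistic as an objective and as an outcome in two time windows. A report of 0 versus 0 could be read as no effect on dosing when the measure was barely able to register one.

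**Working it through.** **Inputs.** From Sample size: compliance of about 0.50 (control) and 0.50 + 0.15 = 0.65 (intervention), 1620 infants per arm, 24 clusters of 135 (12 per arm, taking 1:1 allocation), intra-class correlation 0.055, power 82%, alpha 0.05 (taken as two-sided). From the Background: 27 to 48% of earlier admissions received at least one of the five items. Not given anywhere: the share x of infants who had a chest x-ray but no drug. I assume x between 0 and 0.10.

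**1. The plan's own figure.** Design effect = 1 + (135 − 1) × 0.055 = 8.37. Effective size per arm = 1620 / 8.37 = 193.5. Standard error of the difference = √[(0.50 × 0.50 + 0.65 × 0.35) / 193.5] = 0.0497, and 0.15 / 0.0497 = 3.02. A t-test with 12 + 12 − 2 = 22 degrees of freedom gives 82.3% power, which agrees with the stated 82%. So 50% and 65% are indeed the rates behind the design.

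**2. Share with no drug dose, first 24 h.** Zero-drug share z = compliance + x, so z cannot be below compliance.

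- Control: z ≥ about 0.50, so at most about 50% have any dose.
- Intervention: z ≥ about 0.65, so at most about 35% have any dose.
- For any single drug, the share with no dose is at least as large as z.

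**3. How firm the zero is.** The observed median for any drug exceeds 0 if the observed zero-drug share falls below one half. Its chance is Φ[(0.5 − z) / √(z(1 − z) / 193.5)], assuming the correlation of 0.055 also applies to this share.

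| x (assumed) | z, control | chance median > 0 | z, intervention | chance median > 0 |
|---|---|---|---|---|
| 0 | 0.50 | 50% | 0.65 | below 0.001% |
| 0.02 | 0.52 | 29% | 0.67 | below 0.001% |
| 0.05 | 0.55 | 8% | 0.70 | below 0.001% |
| 0.10 | 0.60 | 0.2% | 0.75 | below 0.001% |

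If control compliance is below 50%, x must fill the gap for the expected median to be 0: 0.50 − 0.48 = 2 points at 48%, and 0.50 − 0.45 = 5 points at 45%.

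**4. Total hospitalisation.** Use over the whole stay is at least as high as in the first 24 h, so the Sample size assumption puts no ceiling on it. The only relevant figure is in the Background: 1 − 0.48 = 52% to 1 − 0.27 = 73% of earlier admissions had none of the five items. That points to a median of 0. It describes admissions at seven earlier sites, however, while this trial also samples infants sent home from ED.

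**5. What the median can respond to.** Let q = 1 − z be the share given any drug, and μ the mean doses among them. Mean doses per presentation = q × μ. While q is below one half in both arms, the median is 0 for every value of μ. Halving μ halves the mean and leaves the median difference at exactly 0. On the boundary, the median becomes positive only when q passes one half. That is a fact about whether drugs were used, which the compliance outcomes already measure.

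**The case against.** The strongest reply is that the protocol fixes neither the denominator nor the test, and defers the detail of secondary analyses to a separate SAP that is not shown. Any use of each drug is already a separate outcome in both windows, so a median among recipients, as a measure of intensity, is a plausible reading. That median is at least 1 by definition. A rank-based or count analysis of the extracted doses could also find a difference with both medians at 0.

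A reader might go further than the documents allow and infer that the median is certain to be 0 in both arms and that the outcome cannot show any effect, whatever happens to drug use. That does not follow, for three reasons. The control assumption is only close to 50%, and the x-ray-only share is not given, so the control median for any drug is on the boundary. The 50% and 65% figures cover only the first 24 h. Drug use itself is captured by the primary outcome and the per-drug compliance outcomes, beside which 0 versus 0 would be less likely to mislead.

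These points limit the concern but do not remove it. The choice of the median is made in the protocol itself, not left to the SAP. The recipients-only reading compares groups selected after randomisation by the very behaviour that the intervention targets. A rank test that found a difference would still stand beside a median difference of 0, with no usable effect size.

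**Conclusion.** The point holds in a limited form. Over all presentations in the first 24 h, the expected median is 0 in the intervention arm, and 0 or on the boundary of 0 in control. Medians for single drugs are expected to be 0 in both arms. For total hospitalisation the same conclusion is likely, but rests only on the earlier-trial figure of 27 to 48%.

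It depends on control compliance being about 50%, on the sought 15-point increase, and on an x-ray-only share that the document does not give; the chance of a positive control median runs from 50% to 0.2% as that share goes from 0 to 10%. On neither reading of the denominator does the median give a sound randomised comparison of dosing. This is minor: it touches one secondary outcome, and neither the primary outcome nor the sample size.

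**What to change.** Define the outcome over all sampled presentations. Replace the median as the effect measure with mean doses per presentation, separately for each drug and in each of the two windows. Compare arms with a count model suited to excess zeros (for example negative binomial or hurdle) with a random site effect, and report a rate ratio and a mean difference. Give doses among treated infants as description only. A total pooled across the four drugs is optional and hard to interpret, since a dose of one is not comparable with a dose of another.

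The cost is a change of wording in Research objectives, Research outcomes and the SAP. Dose counts are already being extracted, so no new data are needed. The small downside is that a skewed count has to be modelled.
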